### Ethic declaration

All procedures in the DIMOSI study will comply with the ethical standards of the relevant national and institutional committees on human experimentation. Ethical approval was obtained from the Ethics Committee of the Guangdong Provincial People’s Hospital (KY-Z-2022–002-01), and each collaborating institution also secured approval from its respective Research Ethics Committee. The current study will be conducted in accordance with the Declaration of Helsinki.

### Consent to participate declaration

Every human participant provides their consent prior to enrollment.

### Study population

To determine the subtypes of insomnia disorder and explore their predictive value for trajectory and intervention outcomes, an estimated 40–80 variables will be included in the statistical model. Based on an estimated events per variable (EPV) of 50 to ensure sufficient statistical power, a total of 4,000 participants are required at the baseline [28].

Participants aged 18–65 years with a lifetime history or current insomnia disorder will be recruited. Subjects will be included in the study if they meet the following inclusion criteria: a. Previously or currently meeting the diagnostic criteria for insomnia disorder in ICSD-3; b. Ability to read and understand Chinese, and use the devices required for the study; c. Ability to provide informed consent. The exclusion criteria are: a. Lifetime history of schizophrenia, intellectual disability, or severe physical illness; b. Pregnancy or lactation; c. current involvement in other clinical research projects.

As of June 2025, 33 study sites specializing in psychiatry, neurology, or sleep medicine have taken part in the current study. The principal research centre of the DIMOSI study is located at the Guangdong Mental Health Centre, Guangdong Provincial People’s Hospital (Guangdong Academy of Medical Sciences), Southern Medical University, Guangzhou, China. Additionally, 33 study sites across various regions of China have joined as collaborative institutes (Fig. 2).

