**Methods:**

A total of 4,000 adult participants meeting International Classification of Sleep Disorders, 3rd Edition (ICSD-3) criteria for insomnia disorder will be recruited from community or clinical settings. Eligible participants will be invited to complete the multi-dimensional assessments via a digital platform, including a structured interview, questionnaires, cognitive tasks, sleep-activity diary, physiological characteristics, and ecology momentary assessments, as well as 7-day physical activity and sleep tracking using wearable devices. All participants will be followed up at 6 and 12 months. The primary outcome is the identification of multi-modal subtypes of insomnia disorder and their correlates. Secondary outcomes include the longitudinal trajectories of these subtypes, associated risk factors, and mental health outcomes.

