#### Longitudinal modeling

We will use classification and regression methods to investigate whether baseline information can predict follow-up outcomes. Chi-square analysis, repeated measures analysis, and mixed-effects models will be employed to examine the relationships among the cross-sectional data and the changes over time across different visits. For binary outcomes (e.g., the occurrence of anxiety or depression), logistic regression models will be used, while linear regression models will assess continuous outcomes (e.g., changes in the Insomnia Severity Index (ISI) score). Mixed-effects models will analyze longitudinal changes while accounting for individual variability.

Statistical methods may be adjusted as needed based on the actual data, and we will adopt the most appropriate methods for the analyses. Any limitations in the analysis will be thoroughly addressed and elaborated upon in subsequent research publications.

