## Results

In the current study, 127 researchers across study sites received consistent training in clinical interviews, the use of wearable devices, and other psychological assessments. We randomly selected 46 researchers to complete a reliability assessment for 8 clinical structural interviews. The Cochran’s Q values ranged from 29.2 to 43.0, with all p-values > 0.05, indicating a high consistency among interviewers.

From November 28, 2022, to June 30, 2025, approximately 5000 individuals with suspected insomnia disorder were screened. A total of 3134 participants were interviewed, of whom 2937 (93.7%) were recruited and 197 (6.3%) were excluded. Among those recruited, there are 1743 (59.3%) from outpatient clinics and 1194 (40.7%) from community settings. The most common reason for exclusion was psychotic symptoms resulting from other mental disorders, which led to the inability to complete the clinical interview. The recruitment procedure is shown in Fig. 3.

All participants met the ICSD-3 criteria for insomnia disorder, with a mean age of 37.3 ± 12.6 years and 1952 (66.5%) were females. At baseline, 2850 participants (97.1%) were suffering from current insomnia disorder as defined by the clinical interview based on ICSD-3. In terms of comorbidities, assessed by the structured clinical interviews administered via the Zhiyoumian-Researcher app, 505 participants (17.2%) had current depressive disorders, and 613 participants (20.9%) had current anxiety disorders. The mean score of the ISI was 15.5 ± 5.8, with a median (interquartile range) score of 16.0 (7.0). When comparing those from the community setting and clinic, we found that the participants from the clinic are significantly older than their counterparts. But there is no statistical difference in sex, comorbidities, and insomnia severity (Table 2).

**Table 2 Tab2:** Demographics, comorbidities, and insomnia severity in participants from community and clinic settings（*N* = 2937）

	Community(*n* = 1194)	Clinic（*n* = 1743）	*p*
Age, mean±SD	35.9±12.3	38.2±12.3	＜0.001
Gender Female, n(%)	780 (65.3%)	1172 (67.2%)	0.283
Comorbidities, n(%)	364 (30.5%)	484 (27.8%)	0.115
Depressive Disorder	212(17.8%)	293(16.8%)	0.518
Generalized Anxiety Disorder	270(22.6%)	343(19.7%)	0.058
Bipolar Disorder	39(3.3%)	48(2.8%)	0.439
Panic Disorder	15(1.3%)	25(1.4%)	0.748
Post-Traumatic Stress Disorder	25(2.1%)	45(2.6%)	0.460
ISI, mean±SD	15.7±5.84	15.3±5.79	0.101
ISI ≥ 8, n(%)	1104(92.5%)	1602(92.9%)	0.625

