Research has found that insomnia disorder is a 24-hour condition [80], encompassing not only nighttime sleep disturbances but also daytime cognitive decline and alterations in circadian and activity patterns [81–83]. In our study, we used accelerometers and wearable EEG devices as objective assessment tools to measure sleep quality and rest-activity patterns. We did not use PSG because it is time-consuming and labor-intensive, and one single-night PSG assessment may not adequately capture the day-to-day variations in sleep conditions. We did not include biological sample (e.g., cortisol and melatonin) tests because of lacking reliable biological markers for insomnia disorders currently. Excluding biological samples does not affect our ability to test the research hypotheses.

This promising insomnia cohort, with a target sample size of 4,000, aims to provide sufficient statistical power for subtyping insomnia disorder. Additionally, we collect a series of objective multimodal data. Compared to previous studies using accelerometers to assess the sleep phenotype [84, 85], the current study offers insights into clinical and subthreshold symptoms, as well as cognitive functions [86, 87], which have potential clinical implications. In addition, the current cohort has the potential to clarify the associations of insomnia with other medical conditions and their underlying shared mechanism, enhancing the identification of at-risk individuals and prevention development. For example, given the established bidirectional relationship between insomnia and suicidality, the identification of distinct insomnia subtypes holds significant broader implications [88, 89]. Therefore, this study is likely to fill the knowledge gap in the understanding of insomnia disorder, particularly in the area of clinical subtyping.

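### The target of 4,000 is 50 participants per variable, not 50 events per variable: it gives no basis for the subtyping power claim and does not deliver an EPV of 50 for depression or anxiety

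*Protocol article*

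**What the plan says.** The sample-size paragraph (Study population) says that "an estimated 40–80 variables will be included in the statistical model", to find the subtypes and to study their predictive value for trajectory and intervention outcomes. It then concludes: "Based on an estimated events per variable (EPV) of 50 to ensure sufficient statistical power, a total of 4,000 participants are required" at baseline. No event, event proportion or allowance for loss enters this calculation.

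The Discussion repeats the claim for one aim in particular, describing a cohort that, "with a target sample size of 4,000, aims to provide sufficient statistical power for subtyping insomnia disorder".

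Three other places bear on this:

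- **Primary outcome (Abstract, Methods):** "The primary outcome is the identification of multi-modal subtypes of insomnia disorder and their correlates". Subtyping procedures carries this out by PCA followed by K-means clustering.
- **Follow-up models (Longitudinal modeling):** "For binary outcomes (e.g., the occurrence of anxiety or depression), logistic regression models will be used". Linear regression is planned for continuous outcomes such as change in the ISI score, and mixed-effects models for change over time.
- **Baseline comorbidity (Results):** "505 participants (17.2%) had current depressive disorders, and 613 participants (20.9%) had current anxiety disorders".

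**The concern.** EPV is the number of outcome events divided by the number of candidate predictors. Multiplying an EPV by a number of variables gives a required number of events. The article reports that product as a required number of participants. With 80 variables the two are equal only if every participant has the event.

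This is the only quantitative reason the article gives for the size of the study, and the words about sufficient power rest on it. A reader would credit the clustering with a power basis that EPV cannot give. The same reader would take the prediction models to have 50 events per variable when, for the binary outcomes actually named, they would have far fewer.

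**Working it through.** **Inputs**

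- Variables: 40 to 80; EPV: 50; stated size: 4,000 (Study population).
- Depression 17.2% and anxiety 20.9% (Results). These are baseline prevalences, used as a proxy because the article gives no event rate at 6 or 12 months.
- Other proportions: 5-year persistence of insomnia symptoms 32.6%–42.5%, and poor treatment response about 20%–40% (Background).

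**1. Reproduce the stated figure**

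EPV × variables = 50 × 80 = 4,000, an exact match. The lower end, 50 × 40 = 2,000, does not match. The stated size is therefore 4,000 / 80 = 50 participants per variable.

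**2. Apply the definition of EPV**

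Required participants = EPV × variables / event proportion. With 80 variables this equals 4,000 only if the event proportion is 100%.

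**3. Subtyping**

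PCA and K-means use no outcome variable. There is no event to count, so EPV has no value for this aim, high or low.

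**4. Named binary outcomes, no loss to follow-up**

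Events = 4,000 × proportion; EPV = events / variables.

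| Outcome | Events | EPV, 80 variables | EPV, 40 variables |
|---|---|---|---|
| Depression | 4,000 × 0.172 = 688 | 688 / 80 = 8.6 | 688 / 40 = 17.2 |
| Anxiety | 4,000 × 0.209 = 836 | 836 / 80 = 10.5 | 836 / 40 = 20.9 |

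The delivered EPV runs from 8.6 / 50 = 17% to 20.9 / 50 = 42% of the stated value.

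To show the size of the gap (not as a proposal), an EPV of 50 with 80 variables would need 4,000 / 0.172, about 23,300 participants, for depression and 4,000 / 0.209, about 19,100, for anxiety.

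**5. More frequent outcomes from the Background**

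- Persistence: 4,000 × 0.326 = 1,304 and 4,000 × 0.425 = 1,700 events. EPV is 16.3–21.3 with 80 variables and 32.6–42.5 with 40.
- Poor response: 800–1,600 events. EPV is 10–20 with 80 variables and 20–40 with 40.

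These come closer to 50 but do not reach it.

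**6. Continuous outcomes**

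For linear models of ISI change, participants per variable is a meaningful quantity. With 80 variables it is 50 before losses. Under assumed losses of 10%, 20% or 30% it is 3,600 / 80 = 45, 3,200 / 80 = 40 or 2,800 / 80 = 35.

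**The case against.** The strongest reply is that the multiplication is right and only the label is loose: the authors meant participants per variable. For the linear models that reading is sensible, and this part stands. It also concedes the point, because the printed term is EPV and the power claim for subtyping is drawn from it.

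A second reply is that 80 is inferred. The article gives a range, and 40 variables with an event in half the participants also gives 40 × 50 / 0.5 = 4,000. That is true. It means that a reader who infers that no event outcome could reach an EPV of 50 goes too far: with 40 variables and a plain event count, any outcome affecting at least half the participants would reach it, before losses. The article states no such outcome as the basis, however, and depression and anxiety miss 50 at both ends of the range.

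A third reply is that harm is not shown. A reader might infer that the logistic models will be overfitted. The article does not establish this: it does not say that 40–80 raw variables enter each model, and the predictors may be a few subtype indicators or principal components, which would raise the EPV. The consequence is therefore conditional.

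Fourth, depression and anxiety are given only as examples, and baseline prevalence is not a follow-up event rate. Both are fair. The Background proportions are more favourable but still fall short. One could go further and compute a much lower EPV for new-onset depression, but the article gives neither incidence nor retention, so that figure would rest on assumptions alone and is not relied on here.

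Finally, the sentence cites a source that was not available. It may support a rule based on participants per variable, but that would not turn participants into events. A detailed attrition allowance may properly sit in a full protocol or SAP, and its absence from the article is not the point.

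**Conclusion.** The point holds as an error of label and justification, not of multiplication. The stated 4,000 is 50 participants per variable at 80 variables. It is not an EPV of 50.

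- **Subtyping:** EPV is undefined, so it cannot support the power statement in the Discussion. A reader might conclude that 4,000 is too small for clustering. Nothing in the article shows that; it shows only that the reason given does not bear on the question.
- **Named binary outcomes:** the EPV is about 9 to 10 with 80 variables and 17 to 21 with 40. This assumes that baseline prevalence stands in for occurrence at follow-up, that nobody is lost, and that the full 40–80 variables enter the model. Losses would lower the figures; fewer predictors would raise them.
- **Continuous outcomes:** 50 participants per variable is a usable description, before losses.

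**What to change.** Enrolment need not change.

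1. In Study population, restate the basis as 50 participants per variable at 80 variables, before loss to follow-up, and say that it applies to the continuous-outcome models.
2. Remove the EPV-based power claim for subtyping there and in the Discussion.
3. Give the expected events and the resulting EPV for the named binary outcomes, with the event proportion and retention assumed.
4. If the full 40–80 variables are to enter those logistic models, either limit the predictors to a number the events can support, or use penalised regression and report optimism-corrected performance.

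The cost is a rewritten paragraph, a less favourable stated figure and a little more analysis work.

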**Fig. 2 Fig2:**
[figure not shown]
Geographic distribution of the 33 collaborative study sites across China

All individuals participating in the study are permitted to continue their ongoing treatments and medications, which will be recorded and documented throughout the research. In addition, electronic Cognitive Behavioral Therapy for Insomnia (e-CBTI), a routine fee-based clinical service delivered via a smartphone application, was optionally accessible to participants; for those who opted in, the study team covered the service fee without modifying the treatment content or delivery.

### Study procedures

Each site adopted systematic convenience sampling, screening for all eligible participants from both community and clinical sources who are willing to join the study. Screening logs and reasons for exclusion are documented to evaluate potential selection bias. Standardized recruitment and assessment procedures are implemented uniformly across all participating sites. Figure 3 illustrates the recruitment process for the study. Potentially eligible individuals will be screened through either outpatient clinic or community settings. Research assistants will contact these individuals to provide a brief explanation of the study objectives and conduct a preliminary eligibility assessment. Those deemed potentially eligible will be invited to the nearest study site for confirmation of eligibility and a face-to-face baseline assessment.

**Fig. 3 Fig3:**
[figure not shown]
Flowchart of participant recruitment and screening process

All participants will be invited for follow-up assessments at 6 months and one year after completing the baseline assessments. Participants will receive travel allowance of 80–150 CNY (approximately 12–20 US dollars) for each visit, depending on the completion rate of assessments.

### Digital platform

Data in the DIMOSI are managed through the Zhiyoumian electronic data platform. Developed by the research team, this platform is equipped with capabilities for data collection, preliminary analyses, and management. All assessments in the study—including structured clinical interviews, validated questionnaires, cognitive tasks, sleep-activity diaries, anthropometric assessments, facial expression, and ecological momentary assessment (EMA)—for measuring mental disorders/symptoms, emotions, behaviors, cognitive function, sleep, activity, and other related parameters (Table 1) are integrated into this digital platform. Two apps, Zhiyoumian - Participant and Zhiyoumian - Researcher, were developed for both Android and IOS systems. The platform adopts end - to - end encryption technology to ensure data security.

**Table 1 Tab1:** Assessments in each visit for the DIMOSI

Domain	Assessment approach	Measurement	Baseline visit	FU 1	FU 2
Mental disorders and symptoms	Clinical interview	Mental disorders and their Symptoms [29]	X	X	X
Sleep and Circadian Rhythm	Clinical interview	Diagnostic Interview for Sleep Patterns and Disorders [30, 31]	X	X	X
	Questionnaire	Insomnia Severity Index (ISI) [32, 33]	X	X	X
	Questionnaire	Morning and Evening Questionnaire 5 (MEQ-5) [34, 35]	X	X	X
	Questionnaire	Epworth Sleepiness Scale (ESS) [36, 37]	X	X	X
	Questionnaire	Ford Insomnia Response to Stress Test (FIRST) [38, 39]	X	X	X
	Questionnaire	Dysfunctional Beliefs and Attitudes about Sleep-16 (DBAS-16) [40, 41]	X	X	X
	Questionnaire	Multi-dimensional Fatigue Inventory (MFI) [42, 43]	X	X	X
	Questionnaire	Pre-sleep Arousal Scale (PSAS) [44]	X	X	X
	Questionnaire	Sleep Hygiene Practices Scale (SHPS) [45]	X	X	X
	Questionnaire	STOP-BANG questionnaire (SBQ) [46]	X		
	Questionnaire	Activity Diary (Sleep diary + Social Rhythm measure)	X X	X X	X X
	Monitoring devices	Wearable EEG	X X		X X
	Monitoring devices	Accelerometer	X X		
Emotion	Questionnaire	9-item Patient Health Questionnaire (PHQ-9) [47]	X	X	X
	Questionnaire	Generalized Anxiety Disorder Scale-7 (GAD-7) [48, 49]	X	X	X
	Questionnaire	Beck Scale for Suicide Ideation (BSI) [50, 51]	X	X	X
	Questionnaire	Positive and Negative Affect Schedule (PANAS) [52, 53]	X	X	X
	Questionnaire	Ruminative Responses Scale (RRS) [54, 55]	X		
Cognition	Questionnaire	Attention to Positive and Negative Information Scale (APNIS) [56, 57]	X	X	X
	Questionnaire	Barratt Impulsiveness Scale 11 (BIS-11) [58, 59]	X		
	Digital cognitive tasks	Psychomotor vigilance test (PVT)	X	X	X
	Digital cognitive tasks	Balloon Analogue Risk Task (BART)	X	X	X
	Digital cognitive tasks	Go/No-Go Task	X	X	X
	Digital cognitive tasks	N-Back task	X	X	X
physicality	Facial Recognition	Facial image	X	X	X
	Questionnaire	Short-form McGill Pain Questionnaire-2 (SF-MPQ-2) [60, 61]	X	X	X
	Questionnaire	Patient Health Questionnaire-15 (PHQ-15) [62, 63]	X	X	X
	Medical records	Height	X		
	Medical records	Weight	X		
Life events	Questionnaire	Quality of Life-BREF (QOL-BREF) [64]	X	X	X
	Questionnaire	Childhood Trauma Questionnaire (CTQ) [65, 66]	X		
	Questionnaire	Life Event Scale (LES) [67]	X	X	X
	Medical records	Medical history	X	X	X
	Medical records	Family history	X		
Life style	Questionnaire	Subjective daily pattern (activity, diet, and sleep)	X	X	X
Personality	Questionnaire	Big Five Inventory-2 (BFI-2) [68, 69]	X		
General Health	Ecological momentary assessment	EMA questionnaire, Supplementary Methods, Section 2	X X		
	Questionnaire	General information (Supplementary Methods, Section 1)	X	X	X

X delivered once; XX delivered every day for 7 days; XXX delivered every day according to the therapy

FU: Follow-up assessment

Both apps were evaluated using the System Usability Scale (SUS). The Cronbach’s α of Zhiyoumian–Participant app was 0.82 with a mean SUS score of 66.22 ± 13.41, from 610 recruited participants, while the Cronbach’s α of Zhiyoumian–Researcher app was 0.84 with a mean score of 72.31 ± 15.23, from 53 researchers of study sites, indicating acceptable usability for both applications.

Each participant will be asked to install Zhiyoumian - Participant, while all researchers will install Zhiyoumian - Researcher. Zhiyoumian - Researcher guides researchers through conducting structured clinical interviews based on the Diagnostic and Statistical Manual of Mental Disorders, Fifth Edition (DSM-5) [29] and the International Classification of Sleep Disorders, Third Edition (ICSD-3) [30] to determine the diagnoses of insomnia disorder, comorbidity, and other related information. Zhiyoumian – Participant integrates self-reported information, such as questionnaires and sleep-activity diaries, along with objective data from two wearable devices. Ecological momentary assessment(EMA), an intensive assessment method [70], will be administered four times daily over a consecutive seven-day period, assessing daily sleep, mood, physical activity, diet, and related parameters. Participants who responded to less than 30% of the prompts might be excluded from the EMA-specific analysis. It is designed to collect concise, real-time evaluations of key domains, including sleep, physical activity, emotion, and diet. The wearable EEG monitor (EEG Smart S1) and accelerometer (Axivity, AX3) will be provided to each participant to measure sleep parameters [71], physical activity [72], and other related physiological indicators [73, 74]. The data of the days when the Axivity is worn for less than 16 hours will be excluded. Participants will be included when meeting the criteria as wearing the device at least 16 hours in at least 3 days in the actigraphy analysis. Similarly, data from the wearable EEG monitor will be included only if at least 4 hours of scorable sleep data per night is available, and participants will be included in the analysis when meeting the criteria as wearing the device for at least 1 day. The digital platform benefits the real-time interaction between participants and researchers.

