Significant efforts have been made in recent decades to clarify the diverse manifestations of insomnia disorder. First, the most commonly used classification in general clinical practice is based on nocturnal complaints [2] according to the International Classification of Sleep Disorders - Third Edition (ICSD-3) [7, 13]. Clinicians typically prescribe hypnotics with different half-lives based on difficulty initiating sleep (DIS), difficulty maintaining sleep (DMS), or early morning awakenings. However, over half of patients with insomnia disorder report at least two types of nocturnal symptoms, and the stability of this classification system is often unsatisfactory [8, 14]. Second, Vgontzas and colleagues have found that insomnia with objectively short sleep duration as measured by a single-night nocturnal polysomnography (PSG), may represent a more biologically severe subtype with a diminished response to CBTI compared to insomnia without short sleep duration [15]. However, PSG requires overnight hospitalization, which is costly, time-consuming, and limits scalability [16]. Third, recent studies have attempted to use emotional processing and cognitive functions to subtype insomnia disorder [12], but their application in clinical practice remains underexplored. Finally, a recent effort using portable sleep assessments extracted insomnia-related subtypes from a large-scale cohort, but clinical interpretations of these subtypes were not provided [17].

Taken together, previous studies have proposed several subtypes of insomnia disorder based on subjective and objective measures [18–20]. However, subtyping methods that rely solely on subjective reports are easy to implement but will lack objective indicators, resulting in ambiguous classifications. On the other hand, subtyping based on PSG monitoring is limited in capturing the temporal and spatial fluctuations of sleep in insomnia. Moreover, the current classification schemes for insomnia provide limited guidance for clinical treatment [21]. This classification challenge is closely tied to the high heterogeneity of insomnia disorder. In the current study, we plan to integrate the data of sleep and circadian rhythm, mental distress, behavior, and cognitive function, from both subjective reports and long-term ambulatory monitoring.

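### As worded, the wearable-EEG night rule makes inclusion depend on the hours slept, which overstates EEG sleep time most in short sleepers

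*Protocol article*

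**What the plan says.** The device rules are in the Digital platform section of the protocol article.

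- Wearable EEG, night level: "data from the wearable EEG monitor will be included only if at least 4 hours of scorable sleep data per night is available".
- Wearable EEG, person level: "participants will be included in the analysis when meeting the criteria as wearing the device for at least 1 day".
- Accelerometer, day level: "The data of the days when the Axivity is worn for less than 16 hours will be excluded".
- Accelerometer, person level: "wearing the device at least 16 hours in at least 3 days in the actigraphy analysis".

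Table 1 gives the wearable EEG the mark that its footnote explains as "XX delivered every day for 7 days", at baseline and at the second follow-up. The section on multimodal data integration lists objectively measured sleep among the feature groups for subtyping. The Background reports earlier work in which "insomnia with objectively short sleep duration as measured by a single-night nocturnal polysomnography (PSG), may represent a more biologically severe subtype". The Discussion gives as one reason for not using PSG that "one single-night PSG assessment may not adequately capture the day-to-day variations in sleep conditions".

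**The concern.** A validity rule should separate good recordings from bad ones without looking at the value being measured. The accelerometer rule does this, because hours of wear say nothing about how well the participant slept. The EEG rule, taken at its word, does not. It sets a floor on sleep within the night, so it cannot tell a failed recording from a good recording of a bad night, and it makes no exception for the second.

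The result is left truncation of nightly sleep time. The nights removed are the shortest ones, and they are removed most often from people who sleep least. These are the people who would form the short-sleep group that the Background describes as possibly more severe. Any EEG feature averaged over the remaining nights moves towards normal sleep, and the contrast that the clustering could use is reduced.

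There is a smaller looseness at person level. The minimum is one day of wear, not one valid night, and it is lower than the three days asked of the accelerometer.

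**Working it through.** **The plan's own figure.** EEG uptake in the Results is 2429 of 2937; 2429/2937 = 0.827, which agrees with the stated 82.7%. The plan computes nothing from the 4-hour rule, so there is no further figure to reproduce.

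**Inputs from the article.** Night threshold 4 h; 7 scheduled nights; person-level minimum of 1 for EEG and 3 for the accelerometer; features with more than 30% missingness excluded from the subtyping.

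**Assumptions, not in the article.** Nightly sleep time is normal around a person's true mean μ, with within-person SD σ of 1.0 to 1.5 h and nights independent given μ. The night-to-night intraclass correlation (ICC) is 0.3 to 0.6.

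**Step 1: bias if the 4 hours means sleep.** With a = (4 − μ)/σ, the share of nights dropped is Φ(a), and the mean of the retained nights is μ + σ·φ(a)/(1 − Φ(a)). For μ = 4.5 and σ = 1.0, a = −0.5, the share dropped is 0.309 and the retained mean is 5.01 h.

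| True mean (h) | Nights dropped, σ = 1.0 / 1.5 | Retained mean (h) | Overstatement (h) |
|---|---|---|---|
| 4.0 | 50% / 50% | 4.80 / 5.20 | 0.80 / 1.20 |
| 4.5 | 31% / 37% | 5.01 / 5.40 | 0.51 / 0.90 |
| 5.0 | 16% / 25% | 5.29 / 5.64 | 0.29 / 0.64 |
| 6.0 | 2% / 9% | 6.06 / 6.27 | 0.06 / 0.27 |

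**Step 2: effect on contrast.** Take two people with true means of 4.5 and 6.0 h, a gap of 1.5 h. The observed gap is 6.06 − 5.01 = 1.05 h for σ = 1.0, and 6.27 − 5.40 = 0.87 h for σ = 1.5.

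**Step 3: loss of the whole modality.** The chance of no valid night in 7 is Φ(a)^7. It is 0.03% to 0.09% at a mean of 4.5 h, 0.5^7 = 0.8% at 4.0 h, and 4% to 8% at 3.5 h. The rule therefore acts on nights and on feature values, and seldom on whether a person has EEG data at all.

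**Step 4: one night against several.** By Spearman-Brown, the reliability of a k-night mean is k·ICC/(1 + (k − 1)·ICC). For ICC 0.3 to 0.6 this gives 0.30 to 0.60 for one night, 0.56 to 0.82 for three and 0.75 to 0.91 for seven. One night gives no estimate of within-person variability.

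**Step 5: what a fixed three-night minimum could cost.** To stay within 30% missingness at the current recruitment, a feature needs 0.70 × 2937 ≈ 2056 participants. With 2429 wearers, the margin is 2429 − 2056 = 373, or 15% of wearers. If more than that had fewer than three valid nights, the EEG features would fall out of the clustering.

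**The case against.** The strongest reply is that the phrase need not mean hours of sleep. The rule follows the accelerometer wear rule and is introduced as a parallel to it, so it can be read as asking for 4 hours of data fit to be scored, wake included. A 7-hour recording with 3.5 hours of sleep would then be kept, and the figures in Step 1 would not apply to such nights. This stands as a real alternative. The article does not settle it, and the Results leave detailed cleansing of the objective data to a later report. It does not remove the point, because the wording as published supports the reading that causes bias.

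Three stronger inferences are tempting, and the article does not support them.

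- That short sleepers lose their EEG data. With 7 nights scheduled and one sufficient, this is rare unless mean sleep is below about 4 h (Step 3). Diaries and accelerometry have no such cut.
- That the study falls back on the single-night assessment it criticises. One night is the minimum accepted, while seven are planned. How many participants have only one valid night is not reported.
- That night-to-night variability of sleep duration is a stated clustering input. The article names objective sleep measures in general and does not list this feature.

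It is also fair to say that the share of participants averaging 4 to 5 h is unknown, so no effect on the whole cohort can be given.

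**Conclusion.** The point holds as a fault in how the EEG rule is fixed. Under its literal reading, inclusion of a night depends on the sleep obtained. EEG sleep time is overstated by about 0.5 to 0.9 h at a true mean of 4.5 h, but by only 0.06 to 0.27 h at 6.0 h. The short-sleep contrast is weakened, not abolished. These sizes rest on the assumed nightly SD of 1.0 to 1.5 h, normality, independent nights, and the 4 hours meaning sleep. If it means recording time including wake, the effect is much smaller.

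The one-night minimum is a lesser matter. It mixes values of unequal reliability, but raising it outright could push EEG features past the plan's own missingness limit. That argues for a sensitivity analysis and not for a new primary rule.

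**What to change.** 1. Define a valid EEG night by scorable recording time or signal coverage, with wake epochs counted, independent of hours slept. A cleanly recorded short night is then retained.
2. Keep the minimum of one night for the primary analysis, but word it as one valid night, not one day of wear.
3. Repeat the clustering in participants with at least 3 valid EEG nights as a sensitivity analysis, matching the accelerometer minimum.
4. Report the nights and participants excluded by the rule, by ISI category, and the distribution of valid nights per participant.

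The cost is reprocessing of recordings already held, a change of wording and one additional analysis. No new data collection is needed.
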